## Abstract

Fatigue’s interference with activities, mood, and cognition is one of the most prevalent and distressing problems of patients with advanced gastrointestinal cancer. As fatigue interferes with patient functioning, family caregivers often report feeling burdened by increasing demands. Evidence-based interventions for patient fatigue interference and caregiver burden are lacking in advanced gastrointestinal cancer. In a pilot trial, telephone-based Acceptance and Commitment Therapy (ACT) showed potential for reducing patient fatigue interference and caregiver burden in this population. The current Phase II trial seeks to determine the efficacy of this intervention for patients with advanced gastrointestinal cancer and moderate-to-severe fatigue interference and their family caregivers with significant caregiving burden. In this trial, 244 dyads are randomly assigned to either the ACT intervention or an education/support control. Participants in both conditions attend six weekly 50-min telephone sessions, four of which involve both dyad members, and a 30-min booster session. The primary aim is to test the effects of telephone-delivered ACT on patient fatigue interference and caregiver burden. Secondary outcomes include patient sleep interference and patient and caregiver engagement in daily activities and quality of life. Outcomes are assessed at baseline, 2 weeks post-intervention, and 3 months post-intervention. This trial also examines whether increased psychological flexibility, defined as mindful acceptance of present experiences, including challenges, while pursuing actions aligned with personal values, mediates ACT’s effects on primary outcomes. Our ability to demonstrate ACT’s efficacy will support its adoption in cancer care. Findings will also inform future ACT trials for dyads coping with other serious illnesses.

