The primary aim of this NIH-funded Phase II RCT is to examine the efficacy of our telephone-delivered ACT intervention for patients with advanced GI cancer and fatigue interference and their family caregivers with caregiver burden. We hypothesize that ACT will lead to improved primary outcomes of patient fatigue interference and caregiver burden compared to time-matched education/support. Our second aim is to examine ACT’s effects on the secondary outcomes of patient sleep interference and patient and caregiver engagement in daily activities and QoL. We hypothesize that ACT will lead to improved secondary outcomes compared to education/support. Our third aim is to test the hypothesis that increased psychological flexibility will mediate ACT’s effects on patient fatigue interference and caregiver burden. Our fourth aim is to explore changes in the two core aspects of psychological flexibility (i.e., mindfulness/acceptance and commitment/behavior change processes) as mediators of ACT’s effects on patient fatigue interference and caregiver burden. This paper describes the rationale, study design, methods, and statistical plan.

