We estimated the effect size based on the difference between study conditions on the primary outcomes of patient fatigue interference and caregiver burden at 3 months post-intervention. In our pilot RCT in advanced GI cancer, at 3 months we found a medium effect (*d* = −0.60) of condition (ACT vs. education/support) on patient fatigue interference and a small effect (*d* = −0.18) of condition on caregiver burden [21]. In contrast to our pilot, the current trial has a booster session to maintain ACT’s effects. Minimal clinically important differences (MCIDs) or clinically meaningful changes on the Fatigue Interference subscale of the FSI have been reported for cancer populations (range = 0.39–1.63) [68]. MCIDs in caregiver burden have yet to be determined. Estimates of treatment effects from pilots are imprecise [69,70]; thus, we examined results across relevant ACT trials and recommendations regarding MCIDs [71,72] to inform our power calculation. Although ACT has rarely been studied with cancer caregivers, it had a medium effect (*d* = −0.39) on dementia caregivers’ depressive symptoms – which are strongly correlated with caregiver burden [73] – relative to psycho-education at 6 months post-intervention [74]. Additionally, ACT had medium to large effects on mental health outcomes in a meta-analysis of RCTs for clinical populations [75]. In the absence of an established MCID for a self-report measure, a standardized effect size of 0.30–0.50 is recommended to estimate the MCID [71,72]. Thus, we estimate a moderate effect size of *d* = −0.40 for both primary outcomes. With *N* = 170 dyads at 3 months post-intervention (assuming 30 % attrition), we will have 85 % power (α = 0.05, two-tailed) to detect a Cohen’s *d* = −0.40 in a linear mixed model. The estimated attrition is based on our pilot data [21] and survival rates in advanced GI cancer [76].

### Analysis for aim 2

3.3.

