Linear mixed effects modeling (R lme4) [66] will be used to test the hypothesis that ACT will improve secondary outcomes as compared to education/support. For outcome measures that only patients or caregivers complete, models will include main effects of time (as categorical) and condition and the time-by-condition interaction. Treatment effects will be evidenced by a significant time-by-condition interaction. For outcomes reported by patients and caregivers, multilevel modeling for dyadic data will be used [77,78]. The model will include the main effects of time, condition, and social role (patient vs. caregiver) as well as all two and three-way interactions. The time x condition x role interaction will estimate the degree to which the treatment effect is different for patients and caregivers. The *p* values from the analyses will be adjusted using the Sidak approach to control for the familywise Type I error rate due to correlated multiple secondary outcomes. If treatment effects are significant, follow-up tests (R emmeans) [67] will be performed to examine group differences at each follow-up.

### Analysis for aim 3

3.4.

Cross-lagged panel models in Mplus [79] will be used to test the hypothesis that increases in psychological flexibility will mediate ACT’s effects on primary outcomes (patient fatigue interference and caregiver burden). Outcomes will be examined in separate models that include condition, the mediator (assessed at baseline and 2 weeks post-intervention), and the outcome at all time points. To evaluate model fit, we will use the comparative fit index (CFI) and the root mean square error of approximation (RMSEA), with CFI ≥0.95 and RMSEA ≤0.05 indicating close fit [80]. The indirect effect of condition on each outcome via psychological flexibility will be quantified using the product of the two relevant effects and tested using bootstrapped confidence intervals (CIs) accounting for nonnormality [81]. A total of 10,000 bootstrapped samples will be drawn, and the indirect effect will be considered statistically significant at *p* < .05 if the 95 % CI does not include zero.

### Analysis for aim 4

3.5.

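### The Sidak adjustment of the secondary outcomes is valid, but a step-down (Holm-)Sidak version over the same tests would have more power at the same familywise error

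*Protocol article*

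**What the plan says.** Section 3.3 (Analysis for aim 2) fixes the multiplicity method for the secondary outcomes: p values will be "adjusted using the Sidak approach to control for the familywise Type I error rate due to correlated multiple secondary outcomes". It does not say whether the procedure is single-step or step-down.

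The secondary outcomes are "patient sleep interference and patient and caregiver engagement in daily activities and QoL" (Introduction). That is three measures, two of them completed by both members of the dyad. For the measure completed by patients only, "Treatment effects will be evidenced by a significant time-by-condition interaction". For the shared measures, "For outcomes reported by patients and caregivers, multilevel modeling for dyadic data will be used", and "The time x condition x role interaction will estimate the degree to which the treatment effect is different for patients and caregivers".

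The article states no power for secondary outcomes. Section 3.2 gives 85% power ("α = 0.05, two-tailed") for d = −0.40 with 170 dyads at 3 months, and adopts that effect size "for both primary outcomes" only.

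**The concern.** Single-step Sidak holds every outcome to the strictest threshold, even after other outcomes have been rejected. The step-down version starts at that same threshold and relaxes it after each rejection. It therefore rejects everything the single-step version rejects, and sometimes more, with the same familywise guarantee.

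Aim 2 hypothesises benefit on all the secondary outcomes, which is the situation in which stepping down helps most. If the single-step version is used, some real secondary effects would be missed with no gain in error control.

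**Working it through.** **Inputs from the article.** 170 dyads at 3 months, taken as 85 per arm; d = 0.40 in absolute value; two-tailed α = 0.05 (all section 3.2).

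**Assumptions.** The same d for secondary outcomes; a 5% familywise level for them; equal correlation between test statistics of 0, 0.3, 0.5 or 0.7; families of three (one test per measure) and five (one per measure and role), because the article does not number the family.

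**Plan's own power figure.** For a plain two-group comparison the expected z is 0.40 × √170 / 2 = 2.608, and power is Φ(2.608 − 1.960) = 74.1%. The stated 85% comes from a mixed model whose within-person correlation is not given. With an assumed baseline correlation of 0.50, z = 2.608 / √(1 − 0.25) = 3.011 and power is Φ(1.051) = 85.3%. Both bases are carried forward.

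**Thresholds.** Single-step: 1 − 0.95^(1/m), which is 0.0170 for m = 3 and 0.0102 for m = 5. Step-down, from the smallest p value upwards:
- m = 3: 0.0170, 0.0253, 0.0500
- m = 5: 0.0102, 0.0127, 0.0170, 0.0253, 0.0500

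The first step-down threshold equals the single-step one, so the chance of at least one rejection is identical by construction.

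**Single-step power per outcome.**
- 74% base: Φ(2.608 − 2.388) = 58.7% for m = 3; Φ(2.608 − 2.569) = 51.6% for m = 5.
- 85% base: 72.9% and 66.6%.

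**Gain from stepping down.** Simulation with 400,000 replicates; average points per real effect, ranges over the four correlations:

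| Family | Effects real | Gain, 74% base | Gain, 85% base |
|---|---|---|---|
| 3 | 3 | 7.0–8.7 | 6.4–8.8 |
| 3 | 2 | 2.9–3.6 | 2.8–3.6 |
| 3 | 1 | 0.0–0.2 | 0.0–0.2 |
| 5 | 5 | 8.8–10.2 | 8.7–11.9 |
| 5 | 4 | 5.7–6.3 | 5.7–7.4 |
| 5 | 3 | 3.4–3.7 | 3.4–4.3 |
| 5 | 2 | 1.5–1.7 | 1.5–2.0 |
| 5 | 1 | 0.0–0.1 | 0.0–0.1 |

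On the 74% base at correlations of 0.3 to 0.5, with all effects real, power goes from 59% to 66–67% (three tests) and from 52% to 61% (five tests). At d = 0.30 it goes from 33% to 39% and from 27% to 32–33%.

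**Familywise error.** With no real effects the two versions have the same error: 5.0% at zero correlation, and 4.5% (three tests) or 4.3% (five) at 0.5. With some effects real, step-down uses more of the allowance (for example 4.0% against 3.2% for three tests, one real, correlation 0.5). It stays at or below 5% throughout, within simulation error.

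**Limit of the check.** The simulation uses a single z statistic per outcome, whereas the plan tests a time-by-condition interaction with time as a categorical factor. That step-down never rejects less than single-step holds for any set of p values. The sizes are approximate.

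**The case against.** Four objections deserve weight.

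1. **The step variant is not stated.** The words in section 3.3 could cover step-down Sidak, in which case nothing is lost. This stands. Single-step is the ordinary reading, not a stated fact.

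2. **Sidak is valid here.** A reader might infer that it is misapplied because the outcomes are described as correlated. The article does not support that: positive correlation makes Sidak conservative, and error control is achieved. This stands, and the point is one of efficiency only.

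3. **The gain is conditional.** A reader might take 5 to 10 points as a flat loss. The table shows that it depends on how many effects are real and how large they are, and d = 0.40 was never claimed for secondary outcomes. This stands.

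4. **The family could be three or five.** A reader might infer that its size is open to choice once p values are known. The article does not show this. The list of tests is detail that an analysis plan, not shown here, may settle, and the role interaction is described as estimating heterogeneity. Nor does the ambiguity justify replacing the planned tests with five role-specific 3-month contrasts. That would change the hypotheses and give back most of the gain: against single-step over three tests, step-down over five moves power only from 59% to 61% at d = 0.40, and from 33% to 32–33% at d = 0.30.

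None of this removes the remaining point. For whichever family is planned, step-down is never less powerful and gives the same familywise guarantee.

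**Conclusion.** The point holds as an efficiency improvement, not as an error in the plan. If single-step Sidak is meant, average power per secondary outcome is about 7 to 8 points (three tests) or 9 to 10 points (five tests) below step-down Sidak, provided all effects are real at about d = 0.40 and correlations are moderate. With four of five real the difference is about 6 to 7 points. With two or fewer of three, or three or fewer of five, it is 0 to 4. The secondary effect size, the correlations and the 5% familywise level are assumptions. The comparison is always within one family size, and no claim about the size of the family is made.

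**What to change.** In section 3.3, replace the general reference to Sidak with the step-down (Holm-)Sidak procedure, applied to the planned time-by-condition tests of the secondary outcomes. Keep those tests and the planned family size, and do not substitute 3-month contrasts.

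The cost is a phrase of analysis wording, to be settled before unblinding, with no new data and no change to sample size or conduct. If step-down was already intended, the change only makes that explicit. The one small downside is that simultaneous confidence intervals matching a step-down procedure are less simple to obtain than those matching single-step Sidak.

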#### Descriptive variables

2.7.4.

Demographic and medical variables are evaluated to characterize the sample and to assess equivalence across study conditions. Caregivers also report their relationship to the patient and whether they live with the patient. Medical comorbidities are assessed at baseline only; all other medical factors are collected at each timepoint. Patients and caregivers complete a checklist of eight or nine chronic medical conditions, respectively [57]. Patient functional status is also measured with a 1-item self-reported ECOG measure [28]. Patient cancer information is collected via chart review. Patients and caregivers also report their physical and mental healthcare use in five domains (e.g., number of emergency room visits, outpatient visits) in the past 3 months at baseline and over the study period (past 2 months and 3 months at first and second follow-ups, respectively) [57,58]. Additionally, participants report prescribed and over-the-counter medications [59,60].

Finally, measures of symptom severity are administered at all timepoints to characterize the sample. For patients and caregivers, fatigue severity is measured with four FSI items [29,30], and sleep disturbance, cognitive concerns, anxiety, and depressive symptoms are each assessed with a 4-item PROMIS measure [39,48,49,61–63]. For patients, incontinence and diarrhea are assessed with 4-item and 6-item PROMIS measures, respectively [64].

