#### Analyses of potential covariates

3.1.2.

*T*-tests and chi-square analyses will be used to examine differences between study conditions on potential baseline covariates (e.g., demographics, medical factors). Any differences will be considered when interpreting results, and factors that differ between groups will be included as covariates in sensitivity analyses.

### Analysis for aim 1

3.2.

Linear mixed effects modeling (R lme4) [66] will be used to test the hypothesis that ACT will improve the primary outcomes of patient fatigue interference and caregiver burden as compared to education/support. The model for each outcome will include the main effects of time (as categorical) and condition (ACT vs. education/support) and the time-by-condition interaction. Time will be dummy coded using two dummy variables, with baseline as the reference group. A treatment effect will be evidenced by a significant time-by-condition interaction. If the treatment effect is significant, follow-up tests (R emmeans) [67] will be performed to examine group differences at each follow-up.

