We will use the same analytic approach, as detailed above for Aim 3, to explore the extent to which changes in mindfulness/acceptance and commitment/behavior change processes mediate the effects of ACT on primary outcomes. Outcomes will be examined in separate models that include condition, both mediators (assessed at baseline and 2 weeks post-intervention), and the outcome at all time points.

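### The Aim 3 and Aim 4 mediation models name no confounders of the mediator-to-outcome path, so if ACT changes flexibility the indirect-effect test can be moderately inflated, although likely confounders are collected at baseline

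*Protocol article*

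**What the plan says.** Section 3.4 (Aim 3) specifies cross-lagged panel models for patient fatigue interference and caregiver burden, as "separate models that include condition, the mediator (assessed at baseline and 2 weeks post-intervention), and the outcome at all time points". Section 3.5 (Aim 4) specifies "separate models that include condition, both mediators (assessed at baseline and 2 weeks post-intervention), and the outcome at all time points". The indirect effect "will be quantified using the product of the two relevant effects and tested using bootstrapped confidence intervals", and "the indirect effect will be considered statistically significant at *p* < .05 if the 95 % CI does not include zero". Neither section names a covariate, a no-confounding assumption or a sensitivity analysis for confounding.

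The only covariate rule is in section 3.1.2: "factors that differ between groups will be included as covariates in sensitivity analyses".

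Section 2.7.4 shows what is available. For patients and caregivers, sleep disturbance, cognitive concerns, anxiety and "depressive symptoms are each assessed with a 4-item PROMIS measure". The stated purpose is descriptive: "measures of symptom severity are administered at all timepoints to characterize the sample". Table 2 lists ECOG for patients only. Section 2.4 stratifies randomization by patient age and patient ECOG. Section 3.6 mentions baseline depressive symptoms only as a possible moderator.

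**The concern.** An indirect effect is the product of the effect of condition on the mediator (a) and the effect of the mediator on the outcome (b). Randomization identifies a. It does not identify b, because nobody is randomized to a level of psychological flexibility at 2 weeks. Anything that drives both 2-week flexibility and 3-month fatigue interference or burden biases b, and the product inherits that bias.

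The rule in section 3.1.2 does not help. A variable can be perfectly balanced between arms and still confound the mediator-outcome relation within arms. The article itself points to a candidate: in justifying the effect size (section 3.2) it says that depressive symptoms track caregiver burden closely. Depressive symptoms are measured at baseline in both members of the dyad but are not in the mediation models.

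At stake is the reading of mechanism. Aim 3 is a stated hypothesis, and the Discussion would take a positive result as agreeing with the ACT model.

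**Working it through.** The article gives no figure for the mediation aims, so there is none to reproduce. The sample size is the article's own: 244 × 0.70 = 170.8, stated as 170 dyads at 3 months, taken here as 85 per arm.

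**Inputs that are assumptions.** One baseline covariate C has residual association r with both the 2-week mediator and the 3-month outcome, after the baseline mediator and earlier outcome values have been accounted for. The effect of condition on the mediator is a, in SD units. The true b is zero.

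**Step 1: the b path.** With unit within-arm variances, omitting C gives an expected b of r × r. Its standard error is about √((1 − r⁴)/167), or 0.077. The chance that b is declared non-zero is Φ(z − 1.96) + Φ(−z − 1.96), with z = r²/SE.

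| r | bias in b | z | b rejected |
|---|---|---|---|
| 0.20 | 0.0400 | 0.52 | 8% |
| 0.25 | 0.0625 | 0.81 | 13% |
| 0.30 | 0.0900 | 1.17 | 21% |

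Simulation gives the same values, and about 5% once C is in the model.

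**Step 2: the planned test.** The plan tests the product, so a must be detected as well. For a = 0.4 SD, SE(a) = √(2/85) = 0.153 and z = 2.61, so a is detected about 74% of the time. Multiplying gives a rough guide: 0.74 × 8% = 6%, 0.74 × 13% = 10%, 0.74 × 21% = 16%. Testing the product itself by simulation (n = 170, 4,000 runs, a Monte Carlo interval in place of the 10,000-draw bootstrap) gives slightly lower rates:

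| Assumed effect on mediator | r = 0.20 | r = 0.25 | r = 0.30 |
|---|---|---|---|
| 0 | at most about 1% | at most about 1% | about 1% |
| 0.2 SD | 2% | 3% | 4% |
| 0.4 SD | 5% | 9% | 14% |
| 0.5 SD | 7–8% | 12% | 19–20% |
| 0.4 SD, C adjusted | 3–4% | 3–4% | 3–4% |

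The product test is conservative. With a = 0.4 SD and no confounding at all it rejects about 3–4% of the time, so that is the baseline for comparison.

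**Step 3: do the lagged values already solve it?** A second simulation used three waves and a stable shared cause, with loading λ on mediator and outcome at every wave (autoregression 0.4, a = 0.4 SD, true b = 0, 2,000 runs; all assumed).

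| Outcome equation | λ = 0.3 | 0.5 | 0.6 | 0.7 |
|---|---|---|---|---|
| First-order lags only | 8% | 37% | 61% | 84% |
| All earlier mediator and outcome waves | 6% | 14% | 19% | 27% |
| The same plus the shared cause | 4% | 4% | 4% | 5% |

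With a = 0, every rate is at or below 4%. If the shared cause is measured with reliability 0.8, the adjusted rate is 6% at λ = 0.6 and 9% at λ = 0.7. Lagged values therefore reduce the bias without removing it, and the same is true of adjustment for an imperfectly measured covariate.

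**The case against.** The strongest reply has four parts.

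*The models already condition on a good deal.* They hold the baseline mediator and the outcome at baseline and 2 weeks, which absorb much of a stable shared cause. This stands, and it is why the expected inflation is moderate. A reader might take the 37–84% rates in step 3 as the plan's error rate. The article does not support that: those rates need first-order lags only and high loadings, and the article does not state which lags are fitted.

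*The b-path rates overstate the error of the planned test.* This also stands. A reader might quote 8%, 13% and 21% as false mediation rates. The decision rule is on the product, for which the rates are about 5%, 9% and 14% at a = 0.4 SD and below 5% when ACT barely moves flexibility. The conditions for inflation are nevertheless those the trial expects, since section 2.5.1 predicts that flexibility will increase.

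*The full protocol or analysis plan may add covariates.* That is possible, and the article does not exclude them. But it states the content of these models, and its one general covariate rule uses a criterion that does not address this bias.

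*The consequence is limited.* A reader might infer that a false Aim 3 result would lead to redesign of the intervention. The Discussion ties refinement, in future trials, to finding that one of the two components of flexibility drives the effect. That is Aim 4, which is labelled exploratory.

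**Conclusion.** The point holds in a bounded form. As described, the Aim 3 and Aim 4 models leave the mediator-to-outcome path open to confounding by variables that the trial already measures, and no rule in the article addresses it. With 170 dyads, a 0.4 SD effect of ACT on the mediator and residual associations of 0.2 to 0.3, false indirect effects rise to roughly 5–14%, against 3–4% with adjustment. With residual associations up to 0.3 and an effect on the mediator of 0.2 SD or less, the test stays below 5%.

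The effect on the mediator and the residual associations are assumptions. The article gives no value for either, and its only documented link, between depressive symptoms and caregiver burden, is unadjusted and has no counterpart for fatigue interference or for the mediators. A reader might also infer that baseline adjustment would make the mediation claim causal. It would not, because measurement error, unmeasured causes and causes arising after baseline, such as disease progression, would remain. The primary efficacy analyses in section 3.2 are not affected.

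**What to change.** In sections 3.4 and 3.5, add a pre-specified baseline covariate set to both the mediator and the outcome equations, defined separately for each outcome because ECOG is recorded for patients only:

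- *Patient fatigue interference:* patient age, patient ECOG, and patient baseline depressive and anxiety symptoms.
- *Caregiver burden:* caregiver age, caregiver baseline depressive and anxiety symptoms, and patient age and patient ECOG as the stratification factors.

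Report a sensitivity analysis giving the residual mediator-outcome correlation that would remove the indirect effect. Word mediation conclusions as conditional on no remaining confounding.

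The cost is a few sentences of analysis text, a few more model parameters and one added sensitivity analysis. No new data are needed. Fixing the list before the data are analysed also prevents covariates from being chosen after the results are seen.
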